### Psycho-Education Programme based on cognitive behavioural therapy principle - active control arm

The Psycho-Education Programme is designed to be comparable to MBCT in level of structure, therapist's contact and attention, with participants required to adhere to an agenda during sessions with homework assignments of similar duration. It will consist of a series of 8 weekly 2-hour sessions. The sessions are based on White's book on Treating Anxiety and Stress [15]. All instructors will be qualified clinical psychologists with training in cognitive behavioral therapy.

### Usual care control (UC)

Usual care refers to primary or community care used by participants. In Hong Kong, the majority of primary care is provided by the private sector with around 20% provided by public outpatient clinics. In general, patients who use public outpatient clinics tend to be older, with chronic conditions and who are from a lower socio-economic status.

As the consultation time is usually short (usually one doctor sees about 40-45 patients in one morning), they may be lack of time to deal with patients who present with emotional problems. As a result, usual care can mean minimal care especially if the patients are from lower socio-economic status. The use of this control is to test the effectiveness of MBCT against minimal intervention. All controls will be offered MBCT after the end of the study for ethical reasons.

Measures at baseline and each follow-up: Subjects' demographic data including age, sex, marital status, education status, personal monthly income, religious belief, and all other outcome measures (described below), use of medication (including psychotropics), and experience with mindfulness and yoga, together with medical history including psychiatric history will be collected by a trained interviewer. After the baseline visit, subjects will be randomized as described above. The fidelity of the intervention will be ensured and monitored by a random review of audiotapes that are recorded during all sessions.

## Outcome measures

These will be measured at baseline and at 8 weeks (end of intervention) and will be repeated at 3 months and 6 months and 9 months after intervention.

### Primary outcome measures

Anxiety symptoms will be measured using the validated Chinese version Penn State Worry Questionnaire [16] and the Chinese version Beck Anxiety Inventory [17]. The use of two validated questionnaire is to improve validity of findings. The Penn State Worry Questionnaire is a measure of worry phenomena and has been demonstrated valid in cross-cultural populations. In a study that examined the factor structure and psychometric properties of the Chinese version of PSWQ, this scale has been shown to have good internal consistency, and both convergent and discriminate validity [18]. The Beck Anxiety Inventory (BAI) is the measure most frequently used to assess the construct of anxiety. It is a popular measure due to its efficient, cost-effective and easy to administer, complete and interpret with good reliability and internal consistency [17].

### Secondary outcome measures

Depressive symptoms will be measured by the validated Chinese version of the Centre for Epidemiological Studies-Depression Scale (CES-D) [19]. Health related quality of life will be measured by the validated Chinese version Medical Outcomes Study Short-Form Health Survey (SF-12) [20]. The SF-12 is a 12-item survey that reports health-related quality of life, including both physical and mental functioning and well-being. It has shown to be a valid measure for measuring health related quality of life in local Chinese population.

"Mindfulness" will be measured by the Five Facet Mindfulness Questionnaire [21].

Health service utilization and medication use: Utilization of health services including visits to primary care doctors (both private and public) and hospitalizations and the number of days of absence from work attributable to anxiety will be recorded at 4 weekly intervals by the trained research assistant using telephone. The frequency and duration of practice of both MBSR and PEG in each group will be documented by a Weekly Homework Form that will be collected each week during class and at 3 month interval until the end of 9 month post intervention. Moreover, medication use including changes in medication will be monitored at 3 month interval. Response rate (enrolment of subjects), retention rate (number and proportion attended each class) of the MBCT and the psycho-education group will be documented.

### Data and statistical analysis

Baseline characteristics of the three groups will be compared by ANOVA test for continuous variables and chi-square test for categorical variables. The baseline factors will include age, sex, medication status, psychological and lifestyle characteristics. Our primary end point is the change of anxiety and worry score (BAI and Penn State Worry Scale) from baseline to the end of intervention. Secondary outcomes included the change in scores of CES-D and SF-12. For primary analyses, treatment outcomes will be assessed by ANCOVA, with change in anxiety score as the baseline variable, while the baseline anxiety score and other baseline characteristics that significantly difference between groups will serve as covariates. A two-sided P value of 0.05 or less will be considered be statistically significant. For secondary analyses, the three groups will be simultaneously taken into the analysis of variance model for repeated measures. The baseline measurement of anxiety symptoms and any significant secondary outcome variables will be entered into the model as a covariate as they are considered to be confounders. Analysis will also be performed on an "intention to treat" analysis.

Since there have been no studies on MBCT with an active control that control for contact time and attention, we need to use the only available study on GAD with an active control by Wetherell et al [22] for sample size calculation. The null hypothesis for this study is that there will be no improvement in the outcome measures in the MBCT group relative to other groups and we will test this hypothesis using a one-sided analysis.

Assuming that the average change of mean score of BAI of patients in MBCT is 5.6 (7.4), in the discussion group is 2.0 (7.4) and that in usual care control is 1.1(7.4) with a 1-sided type I error of 5% and 80% power to detect statistical significant differences between the MBCT and psycho-education group as well as MBCT and usual care control, the required sample size is 76 subjects in each group. We set our enrolment target at 228 subjects.

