**Methods:**

A three armed randomized, controlled clinical trial including 9-month post-treatment follow-up is proposed. Participants screened positive using the Structure Clinical Interview for DSM-IV (SCID) for general anxiety disorder will be recruited from community-based clinics. 228 participants will be randomly allocated to the MBCT program plus usual care, psycho-education program plus usual care or the usual care group. Validated Chinese version of instruments measuring anxiety and worry symptoms, depression, quality of life and health service utilization will be used. Our primary end point is the change of anxiety and worry score (Beck Anxiety Inventory and Penn State Worry Scale) from baseline to the end of intervention. For primary analyses, treatment outcomes will be assessed by ANCOVA, with change in anxiety score as the baseline variable, while the baseline anxiety score and other baseline characteristics that significantly differ between groups will serve as covariates.

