## Research objectives

### Primary Objectives

The primary objective of the study is to evaluate the superior effects of MBCT in reducing anxiety symptoms in patients with generalized anxiety disorder from the community and primary care at 9 months when compared to Psycho-Education Group using cognitive behavioural therapy and Usual Care (UG) groups.

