### Secondary objectives

The secondary objectives of this study are to evaluate the effects of MBCT on:

• Patients' reduction of worry symptoms post intervention at 9 months

• Patients' reduction of depressive symptoms post intervention at 9 months

• Patients' reduction of the use of psychiatric medication post intervention at 9 months

• Patients' increase in quality of life post intervention at 9 months

• Patients' reduction in use of health service post intervention at 9 months

• Patients' reduction in leave of absence from work post intervention at 9 months

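### The primary objective is set at 9 months, but the primary end point and its ANCOVA are set at the end of the 8-week intervention, so the stated primary objective has no primary test

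*Protocol article*

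**What the plan says.** **Primary Objectives.** The aim is to show that MBCT is superior to psycho-education and to usual care in "reducing anxiety symptoms in patients with generalized anxiety disorder from the community and primary care at 9 months".

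**Secondary objectives.** All six items are also set at 9 months, for example "Patients' reduction of worry symptoms post intervention at 9 months".

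**Data and statistical analysis.** "Our primary end point is the change of anxiety and worry score (BAI and Penn State Worry Scale) from baseline to the end of intervention". The same paragraph continues: "For primary analyses, treatment outcomes will be assessed by ANCOVA, with change in anxiety score as the baseline variable". I read the score change there as the dependent variable, since the baseline score is listed separately as a covariate. The repeated-measures analysis of variance is placed under secondary analyses.

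**Abstract, Methods.** The end point is the same as in the analysis section: "Our primary end point is the change of anxiety and worry score (Beck Anxiety Inventory and Penn State Worry Scale) from baseline to the end". The end meant is that of the intervention.

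**Outcome measures.** The visit schedule reads: "These will be measured at baseline and at 8 weeks (end of intervention) and will be repeated at 3 months and 6 months and 9". The last three figures are intervals in months, counted from the end of treatment.

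**Sample size.** The assumed BAI changes are 5.6 for MBCT, 2.0 for the discussion group and 1.1 for usual care, each with SD 7.4. No time point is attached to them.

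**The concern.** The objective says which question the trial is meant to answer, and the primary end point says which result will answer it. Here they lie 9 months of follow-up apart. An effect present when the course ends may fade by the last visit, or one may emerge only later. In either case the two definitions give opposite conclusions, and the article supports calling either of them primary. If this stays open until results are seen, the choice of time point can follow the data.

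**Working it through.** **1. Could the two time points be the same visit?** No. The Outcome measures section identifies 8 weeks as the end of the intervention and places the 9-month assessment 9 months after the intervention. The Methods and Design section lists immediate post-intervention and 9 months post-intervention as separate assessments.

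**2. Is one of them a slip in a single sentence?** It does not look so.

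| Section | Time point | Status given |
|---|---|---|
| Primary Objectives | 9 months | primary objective |
| Secondary objectives (six items) | 9 months | secondary objectives |
| Abstract, Methods | end of intervention | primary end point |
| Data and statistical analysis | end of intervention | primary end point |
| Data and statistical analysis, repeated measures | not specified | secondary analysis |

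The objectives agree among themselves, and so do the two statements of the end point. No section reconciles the two sets.

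**3. Which analysis tests which question?** The ANCOVA sentence names no time point of its own. It takes one from the primary end point defined just before it, which is the end of the intervention. The later visits are left to the repeated-measures model, which is secondary. The primary objective at 9 months therefore has no primary analysis.

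**4. Does the sample size break the tie?** No. The 76 per group is derived from BAI changes with no stated time point. The article has no figure on this particular point to reproduce.

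**5. What would be the error rate if success were claimed at either time?** This is an illustration, not a procedure in the plan.

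Inputs: the two-sided 0.05 rule from the analysis section, applied at each of two time points, for one scale and one pairwise comparison. The correlation r between the two test statistics is assumed, because the article gives none.

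Formula: P(at least one false positive) = 1 − P(|Z1| ≤ 1.96 and |Z2| ≤ 1.96), with Z1 and Z2 standard bivariate normal with correlation r.

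- r = 0: 1 − 0.95² = 1 − 0.9025 = 9.75%
- r = 0.3: 9.5%
- r = 0.5: 9.1%
- r = 0.7: 8.3%

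**The case against.** **The operational choice is already clear.** Only one thing is called the primary end point. It has the same time point in both places, and the primary ANCOVA follows from it. On this view the 9-month wording describes the length of follow-up and is not a second primary end point. This has force: it shows which repair is easiest. It does not remove the conflict, because the sentence that sets 9 months stands under the primary objective and names the comparison to be made.

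**The full protocol or SAP may settle it.** A condensed article may leave the 9-month contrast and the time point of the sample-size assumptions to a fuller document, and I do not count either as an error. But the article states two things that do not agree. A fuller document choosing either one would still contradict part of the published text.

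**Two stronger readings are tempting and not supported.**

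- A reader might infer that the plan's type I error is already inflated above 5%. It is not shown to be, because no section provides for success at either time point. The 8.3% to 9.75% describes a misuse that the ambiguity permits.
- A reader might infer that a 9-month comparison would be underpowered through dropout. The article gives no dropout rate by visit. The Limitations section says only that attrition is likely to be higher in usual care. The answer would also turn on sidedness, since the sample size uses a one-sided 5% error and the analysis rule is two-sided. At an assumed 30% loss, power for the 3.6-point difference between MBCT and psycho-education (5.6 − 2.0) is 81% one-sided and 71% two-sided, one on each side of the planned 80%. I draw no conclusion about power.

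**Conclusion.** The contradiction stands on the text alone and needs no assumption. As written, the primary analysis answers an end-of-intervention question, while the stated primary objective asks about 9 months and gets only a secondary analysis. This decides what the trial's main result is, so it should be settled before outcome data are seen. Either time point is a legitimate design; the fault is that the article names both.

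The only figure attached is hypothetical: a false-positive rate of about 8.3% to 9.75% per scale and comparison. It rests on two-sided 5% tests at both times, success claimed on either, and assumed correlations of 0.7 to 0.

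Whether worry is a primary outcome (end point and outcome sections) or a secondary one (Secondary objectives) is a separate issue and is not decided here.

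**What to change.** Name one primary time point and use it in the Abstract, the Primary Objectives and the Data and statistical analysis section.

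- **Simplest route:** keep the end-of-intervention end point as now written, with both the BAI and the Penn State Worry scale. Rewrite the primary objective to match, and make the 9-month comparison a named key secondary contrast.
- **If 9 months is the real question:** leave the objective as it is, and change the end point in the Abstract and the analysis section so that the primary ANCOVA is of change to 9 months.

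Under either route, state which time point the assumed BAI changes in the sample-size paragraph refer to.

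The cost is wording in the protocol and any SAP. No extra data are needed, because both visits are already scheduled.

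### Baseline anxiety is the only covariate sure to enter a model, so adjustment of CES-D and SF-12 change for their own baselines is not guaranteed, and for PSWQ it is ambiguous

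*Protocol article*

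**What the plan says.** All of this is in the protocol article, mainly under Data and statistical analysis.

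- **Primary end point:** "Our primary end point is the change of anxiety and worry score (BAI and Penn State Worry Scale) from baseline to the end of intervention".
- **Further outcomes:** "Secondary outcomes included the change in scores of CES-D and SF-12".
- **Primary model:** the ANCOVA is to be run "with change in anxiety score as the baseline variable, while the baseline anxiety score and other baseline characteristics"; these last are covariates only where a test finds the groups significantly different on them. The Methods part of the Abstract has the same construction: "with change in anxiety score as the baseline variable, while the baseline anxiety score and other baseline characteristics that significantly differ between groups".
- **Secondary (repeated-measures) model:** "The baseline measurement of anxiety symptoms and any significant secondary outcome variables will be entered into the model as a covariate".
- **Screening of baseline factors:** the three groups are compared by ANOVA or chi-square, and the factors compared include psychological characteristics.
- **What counts as anxiety:** Primary outcome measures places both scales under anxiety: "Anxiety symptoms will be measured using the validated Chinese version Penn State Worry Questionnaire [16] and the Chinese version Beck Anxiety Inventory [17". The end-point sentence, the Abstract and the Secondary objectives name worry separately from anxiety.
- **Availability:** the paragraph on measures at baseline and follow-up, and the opening of Outcome measures, have every outcome scale recorded at baseline.

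**The concern.** The plan analyses change in four scales, but only one kind of baseline value is certain to be in a model, and that is anxiety. A change score is correlated with its own starting value: patients who start high tend to fall further, whatever their arm. Baseline BAI captures only part of this for a depression or quality-of-life scale. If the own baseline is left out, the residual variance is larger than it need be, and a chance difference between arms at baseline passes in part into the estimated effect.

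The conditional routes into the model do not settle this. A between-group test of baseline values is a poor trigger, because the own baseline improves precision whether or not the arms differ, and a non-significant difference can still be large enough to matter. The repeated-measures sentence does not say by which test a secondary outcome variable is to be judged significant.

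At stake are the precision of the CES-D and SF-12 comparisons and a clear definition of the PSWQ model, which is half of the primary end point.

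**Working it through.** **Step 1. Which baseline is certain to be in the model?** The plan gives no figure on this point to reproduce, so the sentences are set side by side.

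| Outcome | Own baseline in the model? |
|---|---|
| BAI | Yes: it is the baseline anxiety score |
| PSWQ | Yes if anxiety score covers both scales (Primary outcome measures); no if it means BAI only (end-point sentence) |
| CES-D | Only if it passes a significance criterion |
| SF-12 | Only if it passes a significance criterion |

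**Step 2. Inputs for the size.** From the article: 76 per group. Assumed, because the article gives no correlations: ρ, baseline to follow-up correlation of the outcome, 0.4 to 0.7; r, correlation of baseline BAI with the outcome's baseline, 0.3 to 0.6; correlation of baseline BAI with follow-up equal to rρ; equal variances at baseline and follow-up, set to 1.

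**Step 3. Variance of the treatment effect on change.**

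- Residual variance of change given baseline BAI only: 2(1−ρ) − r²(1−ρ)².
- Residual variance given the own baseline: 1 − ρ². Under the assumed structure, adding BAI to it changes nothing.

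| ρ | r | BAI only | Own baseline | Ratio | 76 ÷ ratio |
|---|---|---|---|---|---|
| 0.4 | 0.3 | 1.2 − 0.0324 = 1.1676 | 0.84 | 1.39 | 54.7 |
| 0.5 | 0.5 | 1.0 − 0.0625 = 0.9375 | 0.75 | 1.25 | 60.8 |
| 0.6 | 0.5 | 0.8 − 0.0400 = 0.7600 | 0.64 | 1.19 | 64.0 |
| 0.7 | 0.6 | 0.6 − 0.0324 = 0.5676 | 0.51 | 1.11 | 68.3 |

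The ratio equals [2 − r²(1−ρ)]/(1+ρ), which falls as either correlation rises. The first and last rows are therefore the extremes of the assumed range. A different choice (ρ 0.5 to 0.7, r 0.3 to 0.7) gives 1.09 to 1.30.

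**Step 4. Effect of a chance imbalance.** The standard error of a baseline difference between two arms is √(2/76) = 0.162 SD. With no covariate, an imbalance d shifts the change contrast by (1−ρ)d in absolute size. Baseline BAI is always in the model and is expected to differ by rd. Its slope on change is −r(1−ρ), so it absorbs the share r², leaving (1−ρ)(1−r²)d. At d = 0.162:

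- ρ = 0.7, r = 0.6: 0.162 × 0.3 × 0.64 = 0.03 SD
- ρ = 0.5, r = 0.5: 0.162 × 0.5 × 0.75 = 0.06 SD
- ρ = 0.4, r = 0.3: 0.162 × 0.6 × 0.91 = 0.09 SD

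**Step 5. What the imbalance test can let through.** For three arms of 76, with two arms d apart and the third midway, F = 76 × 2(d/2)²/2 = 19d². Setting this to the 5% critical value of about 3.04 gives d = √(3.04/19) = 0.40 SD. An imbalance just below that would not bring the covariate in. After BAI adjustment it would shift the contrast by 0.40 × 0.3 × 0.64 = 0.08 SD to 0.40 × 0.6 × 0.91 = 0.22 SD. This is the limit of what the test can miss, not a typical case.

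**Step 6. Steps 3 and 4 are not additive.** The difference between the two variances in step 3 is exactly (1−ρ)²(1−r²), the variance contributed by the unadjusted own baseline. Steps 3 and 4 describe one loss, seen over repeated trials and within one trial.

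**The case against.** **The article may simply be silent.** The ANCOVA sentence is confined to the primary analyses of anxiety change, and the repeated-measures sentence names no response variable. A model for each outcome is normally left to the full analysis plan. This has weight: the article fixes no covariate set specific to CES-D or SF-12. But it does state a rule for which covariates enter the two kinds of model, and a later plan that follows that rule would keep the gap.

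**Four stronger readings are tempting, and the document does not support them.**

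- A reader might infer that the primary model cannot estimate a treatment effect: with the end-of-intervention score as response and both baseline and change as regressors, the arm coefficient is zero by identity. The article never names that response. It names change as the end point and lists baseline anxiety separately as a covariate, so the sentence holds a labelling slip and the intended model is recoverable.
- A reader might infer that CES-D and SF-12 are not adjusted for their own baselines. No sentence says so. Psychological characteristics are among the screened factors, and the repeated-measures model admits secondary outcome variables if significant.
- A reader might infer that PSWQ change is adjusted only for baseline BAI. Primary outcome measures classes PSWQ as an anxiety measure, and on that reading each scale is naturally paired with its own baseline. If anxiety score means BAI only, the sentence does not describe a PSWQ model at all. Either way this is an ambiguity, not a stated omission.
- A reader might infer systematic bias. Under randomisation there is none.

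**Baseline as a repeated level.** The repeated-measures model might carry each outcome's baseline as one of its time points. Its group-by-time contrast from baseline to a visit is then a change-score comparison, which is not by itself adjusted for the own baseline.

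**Conclusion.** The point holds in limited form. Own-baseline adjustment of CES-D and SF-12 change is not guaranteed and rests on significance criteria; for PSWQ the wording allows two readings; the BAI analysis, on which the sample size is based, is unaffected. Under the assumed correlations, omission inflates the variance of the treatment effect by about 11% to 39%, so that 76 per arm carry the information of about 55 to 68. A one-standard-error imbalance moves the estimate by about 0.03 to 0.09 SD. These sizes rest wholly on assumed correlations and equal variances, and apply only where the own baseline does not enter. The information loss concerns outcomes for which the article sets no power target. The consequence is lost precision and chance-imbalance error. It is worth correcting because the remedy is nearly free and also clears up the mislabelled variable in the primary analysis sentence.

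**What to change.** Reword the ANCOVA sentence in Data and statistical analysis and in the Methods part of the Abstract to this effect: for each outcome (BAI, PSWQ, CES-D, SF-12), change from baseline is the dependent variable, treatment arm is the factor, and the baseline value of that same outcome is a covariate in every model, whatever the result of any between-group baseline test. This also replaces the phrase that calls change a baseline variable.

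Apply the same rule to the repeated-measures model, with the post-baseline visits as the response and the outcome's own baseline as a covariate. Baseline BAI may stay as an additional covariate for the other scales.

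The cost is a few sentences of wording and one degree of freedom per model. No new data are needed, since every scale is already measured at baseline.

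### Beyond the baseline anxiety score, covariates for the primary ANCOVA are picked by significance tests between randomised arms, so chance rather than prognostic value decides the primary model

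*Protocol article*

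**What the plan says.** In the protocol article, the section on data and statistical analysis begins with tests of baseline balance: "Baseline characteristics of the three groups will be compared by ANOVA test for continuous variables and chi-square test for categorical variables". It describes the variables only in broad terms: "The baseline factors will include age, sex, medication status, psychological and lifestyle characteristics". The sentence on the primary ANCOVA then names the baseline anxiety score as a covariate and adds that "other baseline characteristics that significantly difference between groups will serve as covariates". The Methods part of the abstract states the same rule: "other baseline characteristics that significantly differ between groups will serve as covariates".

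The baseline anxiety score is therefore fixed in the model, and every other covariate depends on a test result. No significance level is given for the baseline tests themselves; the only general level in the section is "A two-sided P value of 0.05 or less will be considered be statistically significant". Nothing elsewhere in the article replaces the rule with a fixed set.

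In both places, the sentence on the primary model also calls the change in anxiety score the baseline variable, although that change is the endpoint and the baseline score is listed separately as a covariate.

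**The concern.** The abstract says that "228 participants will be randomly allocated to the MBCT program plus usual care, psycho-education program plus usual care or the usual care group". Under random allocation, any difference between arms in a baseline variable arises by chance, so a test of that difference tests a hypothesis already known to be true. A variable is worth adjusting for if it predicts the outcome, and the baseline test does not measure that. A prognostic variable and an irrelevant one have the same chance, about 5%, of entering the model.

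Two things are at stake. First, the primary model cannot be written down before the data are seen. Because the candidate list is open and the baseline threshold is not stated, two analysts could reach different primary models from the same data. Second, the trial forgoes the precision available from always adjusting for a few variables expected to be prognostic.

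This is a stated rule for the primary analysis, not a detail left to a later document. An analysis plan that followed the article would carry the rule forward, and one that fixed its covariates would contradict it.

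**Working it through.** **The plan's own figure.** The article gives no figure for the covariate rule. Its only related figure is 76 per group, from BAI changes of 5.6 (MBCT), 2.0 (active control) and 1.1 (usual care), SD 7.4, one-sided 5% and 80% power. For the smaller contrast, 3.6 points:

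n = 2 × 7.4² × (1.645 + 0.842)² / 3.6² = 52.2, so 53 per group.

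The stated 76 does not follow from these inputs. That is a separate matter and the present point does not rest on it. Below, 76 per group is taken as the planned size.

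**Step 1: chance that the rule changes the model.** Inputs: k candidate variables (not stated; 5 to 20 assumed), each tested at 0.05 (assumed from the general level), tests independent (assumed). P(at least one enters) = 1 − 0.95^k.

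| k | P(at least one enters by chance) |
|---|---|
| 5 | 23% |
| 8 | 34% |
| 10 | 40% |
| 15 | 54% |
| 20 | 64% |

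Positive correlation between candidates, which is likely among psychological scales, lowers these figures.

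**Step 2: what the rule does to error and power.** Simulation with 10,000 trials per setting, 3 × 76 participants, 8 independent candidates of which one is prognostic (assumed correlation 0.3 or 0.5 with the outcome after baseline adjustment), baseline score always in the model, two-sided 0.05, and an effect of 3.6/7.4 of the residual SD:

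| Model | Type I error, r = 0.3 / 0.5 | Power, r = 0.3 / 0.5 |
|---|---|---|
| Baseline score only | 4.9% / 4.9% | 84.6% / 84.2% |
| Test, then adjust | 4.8% / 4.6% | 84.6% / 84.8% |
| Prognostic variable fixed in advance | 5.0% / 5.0% | 87.6% / 93.0% |

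The prognostic variable was selected by the rule in about 5% of trials.

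**Step 3: precision forgone, analytically.** Inputs: difference 3.6 and SD 7.4 (article), 76 per group, and an assumed share R² of residual variance explained by the added covariates. Power = Φ(3.6/SE − 1.96), with SE = SD × √(2/76) and SD² multiplied by (1 − R²).

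*Taking 7.4 as the residual SD:*
- R² = 0: SE 1.200, ratio 2.999, power 85.1%
- R² = 0.10: SD 7.02, SE 1.139, ratio 3.161, power 88.5%
- R² = 0.20: SD 6.62, SE 1.074, ratio 3.353, power 91.8%

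The gain is about 3 to 7 points. In sample-size terms, 76/(1 − R²) = 84 to 95 per group.

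*If the baseline score already explains an assumed 20% of the variance of change:*
- R² = 0: SD 7.4 × √0.8 = 6.62, power 91.8%
- R² = 0.10: SD 6.28, SE 1.019, ratio 3.534, power 94.2%
- R² = 0.20: SD 5.92, SE 0.960, ratio 3.749, power 96.3%

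The gain is about 2 to 5 points. The second case may be closer to the planned analysis, because the article gives 7.4 as the SD of change before any adjustment.

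**The case against.** The strongest case against the point is that the harm is modest. The baseline anxiety score is always in the model. In the simulation the rule loses essentially nothing against an ANCOVA on the baseline score alone, so what is at issue is a possible gain not taken. This stands, and it limits the size of the point.

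A reader might infer that letting the data choose the covariates makes the primary test anticonservative. The calculations do not support that: simulated type I error is 4.6% to 4.8%, slightly below nominal.

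A reader might also infer that the rule omits established predictors such as medication status or depression. The article does not say that either predicts change in anxiety. It lists medication status as a baseline factor and the CES-D as a secondary outcome. They can serve only as examples of candidates for the sponsor to judge.

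The power figures depend on assumed values, and the article itself mixes a one-sided sample-size calculation with a two-sided test. On the one-sided basis, power at 76 per group is already 91%, leaving less room for gain. This too stands, so the figures are best read as ranges. Calling the change score the baseline variable is plainly a slip for the dependent variable. It needs correcting but adds no weight to the point.

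None of this defends the rule itself. It still selects on chance and leaves the primary model open.

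**Conclusion.** The point holds and should be acted on, but it does not threaten the validity of the trial. The primary model, apart from the baseline anxiety score, is set by chance imbalance.

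The share of trials in which at least one covariate enters by luck, 23% to 64%, rests on the assumed number of candidates, their independence and the 0.05 threshold. The forgone power, roughly 2 to 7 percentage points across the two cases, rests on an assumed R² of 10% to 20% and on how much the baseline score already explains. The conclusion that the rule selects without regard to prognostic value needs none of these assumptions, only that allocation is random.

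**What to change.** Remove the rule that ties covariates to baseline significance tests, in both the analysis section and the abstract, and report baseline tables descriptively.

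State the primary ANCOVA separately for each primary measure, BAI and the Penn State worry score. The dependent variable is the change from baseline (or the follow-up score), which also replaces the mistaken reference to a baseline variable. The covariates are that measure's own baseline score plus a short list named now, from data already collected and judged prognostic by the sponsor; medication status and baseline CES-D are examples.

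The model should refer to the primary time point once the sponsor has reconciled the end of intervention (analysis section) with 9 months (primary objective), which is a separate matter.

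The cost is one paragraph and no additional data. The downside is a few degrees of freedom, and little gain if the chosen covariates prove only weakly prognostic.
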